#### Economic evaluation

An economic evaluation will be performed from the societal and the healthcare perspective and will assess the cost-effectiveness of e-Exercise LBP compared to usual physiotherapy at 12 and 24 months.

##### Identification, measurement and valuation of costs

When the societal perspective is applied intervention, healthcare, informal care, unpaid productivity, and paid productivity costs will be included. When the healthcare perspective is applied, only costs accruing to the formal Dutch healthcare sector will be included. The costs of e-Exercise LBP will be estimated using a bottom-up micro-costing approach [76]. Information on the patients’ other kinds of resource use will be collected using eight 3-monthly retrospective cost questionnaires with 3-month recall periods. Healthcare utilization, unpaid productivity, and informal care will be valued in accordance with the “Dutch Manual of Costing” [77]. Paid productivity losses comprise of absenteeism (i.e. sickness absence) and presenteeism (i.e. reduced productivity while at work). Absenteeism was measured using a modified version of the IMTA Productivity Cost Questionnaire (iPCQ). Absenteeism will be valued in accordance with the “Friction Cost Approach” (FCA), using gender-specific price weights [78, 79]. Presenteeism will be measured using the “World Health Organization – Work Performance Questionnaire” as well as the “Productivity and Disease Questionnaire”, and valued using gender-specific price weights as well [78–81].

##### Measurement and valuation of health-related quality of life

The patients’ health states will be measured using the EuroQol-5D-5L (EQ-5D-5L) [82–85]. This questionnaire comprises of five health dimensions, i.e., mobility, self-care, usual activities, pain/discomfort and anxiety/depression. Per health dimension, patients are asked to indicate their severity level. Health states will be converted into utility values using the Dutch tariff [86] and Quality Adjusted Life Years (QALYs) will be estimated using linear interpolation between measurement points.

##### Statistical analyses

Missing cost and effect data will be imputed using ‘Multivariate Imputation by Chained Equations’ and the results will be pooled using Rubin’s rules [87]. Cost differences (∆C) and effect differences (∆E) will be estimated using LMM, and will be corrected for the same baseline variables as the effectiveness analysis. To account for the highly skewed nature of cost data, bias-corrected and accelerated bootstrapping with 5000 replications will be used to estimate 95% confidence intervals around the cost differences (∆C). Incremental cost-effectiveness ratios (ICERs) will be calculated by dividing the difference in costs by the difference in effects (∆C/∆E). Uncertainty surrounding the ICERs will be graphically illustrated by plotting bootstrapped cost-effect pairs on cost-effectiveness planes and by estimating cost-effectiveness acceptability curves. To test the robustness of the study results, several sensitivity analyses will be performed [88].

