**Methods:**

This paper presents the protocol of a prospective, multicentre cluster randomized controlled trial. In total 208 patients with LBP pain were treated with either e-Exercise LBP or usual care physiotherapy. E-Exercise LBP is stratified based on the risk for developing persistent LBP. Physiotherapists are able to monitor and evaluate treatment progress between face-to-face sessions using patient input from the smartphone application in order to optimize physiotherapy care. The smartphone application contains video-supported self-management information, video-supported exercises and a goal-oriented physical activity module. The primary outcome is physical functioning at 12-months follow-up. Secondary outcomes include pain intensity, physical activity, adherence to prescribed (home-based) exercises and recommended physical activity behaviour, self-efficacy, patient activation and health-related quality of life. All measurements will be performed at baseline, 3, 12 and 24 months after inclusion. An economic evaluation will be performed from the societal and the healthcare perspective and will assess cost-effectiveness of e-Exercise LBP compared to usual physiotherapy at 12 and 24 months.

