#### Effectiveness

The primary purpose of this study is to estimate the effectiveness of e-Exercise LBP for improving physical functioning compared to usual primary care physiotherapy in patients with LBP. The primary analysis time point for the study will be 12 months following baseline, however 3- and 24-month changes will also be evaluated. To evaluate the overall effectiveness of e-Exercise LBP, differences in change scores per group and time period will be estimated on primary and secondary outcomes using linear mixed models (LMM) with random effects to control for correlation within patients and physiotherapists [70, 71]. The three-level hierarchy will exist of repeated measurements (level 1), nested within patients (level 2), nested within physiotherapists (level 3). Analysis will be controlled for baseline variables that have been shown to be related to physical functioning, e.g. age, gender, pain severity scores, duration of pain [72–74].

In addition, a per-protocol analysis that only includes patients of the intervention group which were adherent to the smartphone application and the entire usual care group will be performed. Patients will be considered to be adherent to the smartphone application if they used the application for at least 2/3rd of the duration (i.e. 2 out of 3 week for the “low-risk” profile and 8 out of 12 weeks for the “medium- and high-risk” profile) [35, 75]. Per-protocol analyses will be performed using LMM with the same 3-level structure, and will be controlled for the same variables as the primary analysis.

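### The QALY difference is adjusted for covariates chosen for physical functioning; baseline EQ-5D-5L utility, which is part of the QALY, is not named among them

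*Protocol article*

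**What the plan says.** The Statistical analyses part of the Economic evaluation estimates cost and effect differences with linear mixed models and states that they "will be corrected for the same baseline variables as the effectiveness analysis". The Effectiveness section defines that set as "baseline variables that have been shown to be related to physical functioning, e.g. age, gender, pain severity scores, duration of pain".

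For the outcome itself, the section on health-related quality of life says that "Quality Adjusted Life Years (QALYs) will be estimated using linear interpolation between measurement points". The abstract lists health-related quality of life as a secondary outcome and gives the schedule: "All measurements will be performed at baseline, 3, 12 and 24 months after inclusion". The economic evaluation "will assess the cost-effectiveness of e-Exercise LBP compared to usual physiotherapy at 12 and 24 months". The ICER is obtained by "dividing the difference in costs by the difference in effects".

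The article nowhere names baseline EQ-5D-5L utility as a covariate.

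**The concern.** An interpolated QALY is the area under a utility curve that starts at the baseline value. Baseline utility is therefore a component of the outcome as well as a likely predictor of its other components. If the arms differ in baseline utility, the QALY totals differ even when treatment has no effect.

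The effectiveness model deals with an outcome's own starting value by estimating differences in change scores. That does not carry over. A QALY is a single accumulated total per patient, with no change score to take, so borrowing the covariate list alone leaves baseline utility without any stated handling. The list was also chosen for a different outcome.

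The imbalance need not be pure chance. As Study procedure describes it, practices are randomised, their physiotherapists are trained by arm, and these physiotherapists or their colleagues then tell patients about the study. Recruitment under known allocation can produce systematic differences. At stake are the QALY difference, the ICER and the acceptability curves.

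**Working it through.** **Inputs from the article.** ICC 0.05, average cluster size 5, 104 patients per arm (Sample size calculation); measurements at 0, 3, 12 and 24 months.

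**Assumed inputs, because the article gives none for EQ-5D.** Utility SD 0.20 (range 0.15 to 0.25); slope b of follow-up on baseline utility 0.4 to 0.6, the same at every visit; correlation of pain severity with baseline utility 0.3 to 0.7. No discounting is applied. The 0.5 baseline-to-follow-up correlation that the article uses for the ODI lies in the middle of the slope range but is not an EQ-5D figure.

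**1. The article's own sample size.** The article states no figure for the QALY analysis, so this step only confirms the design effect.
- Per arm before adjustment: 2 × (14.5 × (1.960 + 0.842) / 6)² = 91.68.
- Design effect: 1 + (5 − 1) × 0.05 = 1.2. Repeated-measures factor: 1 − 0.5² = 0.75.
- Total: 2 × 91.68 × 1.2 × 0.75 = 165.02, against 165 stated. With 20% dropout: 165 / 0.8 = 206.25, rounded up to 207, as stated.

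**2. Weights in the QALY.** With linear interpolation, each interval gives half its length in years to each end.
- To 12 months (0/3/12): 0.125, 0.500, 0.375. The follow-up weights sum to 0.875.
- To 24 months (0/3/12/24): 0.125, 0.500, 0.875, 0.500. The follow-up weights sum to 1.875.

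The baseline weight depends only on the first interval being 3 months.

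**3. Size of an ordinary chance imbalance.** SE = SD × √(2 × 1.2 / 104). For SD 0.20 this is 0.0304; for SD 0.15 and 0.25 it is 0.023 and 0.038.

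**4. Shift in the QALY difference for a one-SE imbalance, before any covariate adjustment.** Shift = imbalance × (0.125 + b × sum of follow-up weights).

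| Horizon | b = 0.4 | b = 0.6 |
|---|---|---|
| 12 months | 0.0304 × 0.475 = 0.014 | 0.0304 × 0.650 = 0.020 |
| 24 months | 0.0304 × 0.875 = 0.027 | 0.0304 × 1.250 = 0.038 |

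Over the whole SD range, the shifts run from 0.0228 × 0.475 = 0.011 to 0.0380 × 0.650 = 0.025 at 12 months, and from 0.0228 × 0.875 = 0.020 to 0.0380 × 1.250 = 0.047 at 24 months.

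**5. Credit for the planned pain adjustment.** If pain severity correlates r with baseline utility, and affects later utility only through it, the SD of the remaining imbalance is √(1 − r²) of the original: 0.95 for r = 0.3 and 0.71 for r = 0.7. For SD 0.20 the shifts become:
- 12 months: 0.0144 × 0.71 = 0.010 to 0.0197 × 0.95 = 0.019.
- 24 months: 0.0266 × 0.71 = 0.019 to 0.0380 × 0.95 = 0.036.

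Age, gender and duration of pain may remove a little more. With baseline utility itself in a linear QALY model, the expected contribution of the imbalance is about zero.

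**The case against.** The strongest reply is that this is missing detail in a condensed article. The covariates are introduced as examples, so baseline utility is not excluded. It could even meet the criterion, because EQ-5D-5L covers mobility and usual activities. A separate analysis plan might name it. This stands in part: a reader might infer that the plan adjusts for a closed list that leaves utility out, and the text does not say that. But the article does not leave the matter open either. It fixes a rule whose selection criterion is relation to physical functioning, and an analysis plan that follows the rule has no reason to add utility.

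Three further replies limit the size of the point.
- **Direct transfer.** A reader might infer that the whole baseline difference passes straight into the QALY difference. Only the 0.125 weight does so. The rest depends on an assumed slope, which may weaken by 24 months, and pain severity removes part of it.
- **Few clusters.** A reader might suppose that a small number of practices makes imbalance likely. The article's figures imply 207 / 5, or about 41 practices, so this is not supported. The calculation above does not need it.
- **Precision rather than bias.** Chance imbalance is part of the sampling variation that the bootstrap already shows, so for chance alone the loss is mainly one of precision. This stands. It does not cover systematic differences from recruitment after randomisation, which the bootstrap cannot reveal.

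**Conclusion.** The point holds as a weakness of the stated rule. Baseline EQ-5D-5L utility is not named as a covariate for the QALY difference, although it is collected, forms part of the outcome and is likely to predict the rest of it. A baseline utility difference is then only partly removed, which costs precision and leaves room for bias.

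The shifts of 0.014 to 0.020 QALY at 12 months and 0.027 to 0.038 at 24 months are illustrative upper values for SD 0.20 and a one-SE imbalance before any adjustment. They rest on the assumed SD and slope, and fall to 0.010 to 0.019 and 0.019 to 0.036 if pain adjustment works as assumed.

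A reader might go on to infer that the cost-effectiveness conclusion would change. The article gives no expected QALY difference, cost difference or decision threshold, so that cannot be shown. The primary ODI analysis and the sample size are not affected.

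**What to change.** In the Statistical analyses part of the Economic evaluation, state that the QALY model includes baseline EQ-5D-5L utility in addition to the effectiveness covariates, in the base case and in every bootstrap replicate. The cost is one sentence and one covariate, using data already collected. No change to the design, the schedule or the sample size follows.

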### Timeline

Recruitment of physiotherapy practices began in January 2018. The trial started in July 2018. Until January 2020 patients are able to enrol in the study. The follow-up will last until January 2022. Analysis of short-term effectiveness will start in March 2020, analysis of 12-month (cost-)effectiveness will start in January 2021.

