Recently, the authors’ research group developed e-Exercise LBP, a blended and stratified intervention, in co-creation with patients, physiotherapists and experts [33]. E-Exercise LBP consists of face-to-face physiotherapy treatment, in which eCoaching is integrated using a smartphone application. E-Exercise LBP aims to improve patients’ physical functioning by offering a blended stratified-care approach, and consequently influencing patients’ self-management skills and adherence to exercise and physical activity recommendations in a positive way. At the long-term, e-Exercise LBP could result in an improved handling of recurrent LBP and direct and indirect costs. This blended care intervention is an adapted version of previously developed and evaluated blended physiotherapy programs [34, 35]. A pilot study using a prototype of the e-Exercise LBP intervention in 41 patients with LBP demonstrated feasibility and proof-of-concept on functional disability and pain [33]. Based on the results of the pilot study and end-user (patients and physiotherapist) usability experiences, the e-Exercise LBP program was further improved in preparation for the current study.

This study aims to investigate the short- (3 months) and long-term (12 and 24 months) effectiveness on physical functioning and cost-effectiveness of e-Exercise LBP, a primary care based personalized stratified blended care intervention, in comparison to usual primary care physiotherapy in patients with non-specific LBP.

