Because the study design is well-considered, several potential operational issues are taken into account. An important operational issue is the physiotherapists’ training in the e-Exercise LBP intervention. From previous studies we learned that implementing a blended intervention into daily routine is a complex process that changes existing routines [28]. Therefore, training of the participating physiotherapists in the e-Exercise LBP intervention has been expanded from a 4-h training session to two 4-h training sessions. Additionally, Siilo, a secure messenger for healthcare professionals to communicate and share information, will be used during the study to be able to provide direct assistance to participating physiotherapists. And finally, instruction videos were created to support physiotherapists in using the e-Exercise LBP intervention. Another important operational issue is the possible increased risk of drop-outs during this study due to the 24-month follow-up period and the 11 questionnaires that have to be completed during this period. To minimize this risk, a researcher (TK or RA) will conduct the follow-up assessments at 3, 12 and 24 months in person, i.e. by phone, Skype or face-to-face. A final operational issue is the belief that e-Exercise LBP will not provide a solution for all patients having LBP, nor for all physiotherapists treating patients with LBP. Therefore, selection bias could occur, e.g. participants or physiotherapists having low digital literacy skills, or have a more negative attitude towards technology in general, are less likely to be included in this study.

However, with respect to our digitalized society it is expected that the majority of patients with LBP can benefit from the e-Exercise LBP intervention. The results of this study will help to understand whether blended physiotherapy for patients with LBP can be implemented on this basis.

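### The 3-month analysis is dated March 2020, but patients enrolled in January 2020 do not reach 3 months until April 2020

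*Protocol article*

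**What the plan says.** All the calendar dates are in the Timeline section of the protocol article. On the start of the study: "The trial started in July 2018". On enrolment: "Until January 2020 patients are able to enrol in the study". On the end of observation: "The follow-up will last until January 2022". On the analyses: "Analysis of short-term effectiveness will start in March 2020", and "analysis of 12-month (cost-)effectiveness will start in January 2021".

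The meaning of short-term is fixed elsewhere. The aim at the end of the Background refers to "short- (3 months) and long-term (12 and 24 months) effectiveness on physical functioning". The Methods part of the abstract sets the clock: "All measurements will be performed at baseline, 3, 12 and 24 months after inclusion". The 3-month assessment is therefore counted from each patient's own inclusion.

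**The concern.** The dates cannot all hold. Enrolment that runs into January 2020 produces 3-month assessments that run into April 2020, yet the analysis of those assessments is set to begin in March. A team working to the printed date would compare the arms at 3 months before the last-enrolled patients had been measured.

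The stake is information. The missing patients would be absent for purely administrative reasons, so bias is not the main worry. But values due within weeks would be given up for no benefit, on top of the dropout the sample size already allows for. The comparison of dropouts with non-dropouts described under Statistical analysis would also be muddied if patients not yet due were counted as lost.

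**Working it through.** **Inputs (protocol article).** Trial start July 2018, enrolment until January 2020, 3-month analysis from March 2020, 12-month analysis from January 2021 and follow-up until January 2022 (Timeline); 208 patients (abstract, Methods); 20% expected dropout (Sample size calculation). No days of the month and no accrual pattern are given, so both are varied or assumed below.

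**Step 1: check the dates that fit.**
- January 2020 + 12 months = January 2021, the stated start of the 12-month analysis.
- January 2020 + 24 months = January 2022, the stated end of follow-up.

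Both agree, month for month, with enrolment ending in January 2020.

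**Step 2: apply the same rule at 3 months.** January 2020 + 3 months = April 2020. The stated date is March 2020. By day, the last 3-month due date is 1 April if enrolment closed on 1 January and 30 April if it closed on 31 January. On the most lenient reading, with the last patient enrolled on 31 December 2019, it is 31 March.

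**Step 3: size of the gap.** Assume even accrual. A 3-month value is due by the analysis start only if the patient enrolled at least 3 months earlier. The share not yet due is:

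(days from [analysis start − 3 months] to end of enrolment) ÷ (days from trial start to end of enrolment)

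The 3-month cut-off is 1 December 2019 for a 1 March start and 31 December 2019 for a 31 March start. With a trial start of 1 July 2018:

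| Enrolment closes | Last 3-month due date | Not yet due, 1 March start | Not yet due, 31 March start |
|---|---|---|---|
| 31 Dec 2019 | 31 Mar 2020 | 30/548 = 5.5% (11 of 208) | 0/548 = 0% (0) |
| 1 Jan 2020 | 1 Apr 2020 | 31/549 = 5.6% (12) | 1/549 = 0.2% (0) |
| 15 Jan 2020 | 15 Apr 2020 | 45/563 = 8.0% (17) | 15/563 = 2.7% (6) |
| 31 Jan 2020 | 30 Apr 2020 | 61/579 = 10.5% (22) | 31/579 = 5.4% (11) |

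A later trial start shortens the enrolment window and raises the share slightly. With a start on 31 July 2018, a close on 31 January 2020 and analysis from 1 March, it is 61/549 = 11.1% (23 of 208). The full range is about 0 to 11%, or 0 to 23 patients.

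**Step 4: what that costs in precision.** At the upper end, 208 − 23 = 185 patients could have a 3-month value. Treating patients as independent, the standard error grows by a factor of √(208/185) = 1.06, or about 6%. A 20% dropout applied equally to both counts leaves that ratio unchanged. Clustering within practices makes the increase smaller, because losing patients within practices does not reduce the between-practice part of the variance.

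**The case against.** The best defence is that the article gives months rather than days and says only that the analysis will start. No data cut-off or database lock is set. March could mean cleaning and preparation, with the comparison itself run later. January 2020 is a latest date for enrolment, and enrolment may have closed sooner; the abstract already speaks of the 208 patients in the past tense. On those readings the loss may be nil, and the lower end of the range above is indeed zero. This limits the size of the problem but does not reconcile the dates: nothing in the text says that March is preparatory, and even a close on 31 December leaves the last assessment due on the final day of March.

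A reader might go further and infer several things that the document does not support.

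- **That patients not yet due would be imputed.** The Statistical analysis section imputes missing data, but it does not say that this extends to values not yet due.
- **That the early result would contaminate the 12-month primary outcome through unmasked assessors.** The Discussion says that a researcher "will conduct the follow-up assessments at 3, 12 and 24 months in person", meaning by phone, Skype or face-to-face. The article does not say whether that researcher knows the allocation or will see 3-month results by arm. The disability score is collected by online questionnaire (Measurements), so the researcher conducts the contact and does not rate the outcome. A condensed article may leave masking to the full protocol.
- **That more than half of the 12-month assessments would still be outstanding.** Under even accrual the figure is about 50 to 61%, but no accrual pattern is given, and front-loaded enrolment would lower it.

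**Conclusion.** The March 2020 date is wrong on the plan's own figures. It precedes the last 3-month due dates by up to about two months if enrolment runs through January 2020, whereas the 12- and 24-month dates follow correctly from the same close of enrolment. The consequence is conditional: if the comparison is run on the data available in March, about 0 to 11% of 3-month values (0 to 23 of 208) are not yet collected, assuming even accrual and depending on the unstated days.

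The severity is low. Three months is a secondary time point, the missingness would be administrative, and the 12-month primary analysis is not shown to be affected. The documents do not support a finding of bias in the primary outcome, nor a demand to withhold results by arm or to bring in a separate analyst.

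**What to change.** In the Timeline section, replace the March 2020 date with a rule: the 3-month analysis starts only after the last enrolled patient's 3-month assessment is complete. If enrolment runs through January 2020, that is not before the end of April 2020. If enrolment closed earlier, state the actual closing date so that the analysis date can be checked against it. If March was meant only for data preparation, say so and give the date from which the arms are compared.

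The change is one corrected date and one sentence. Its cost is a short-term report one to two months later; the 12- and 24-month dates need not move.
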